1. **Project summary**

Warfarin is a drug that has a narrow therapeutic range and shows individual differences in dose-response, and is influenced by various factors of patients such as interaction with various drugs, diet, and disease state. The anticoagulant effect can change, which is why the drug needs special monitoring. INR is ideal for being within the therapeutic range, but there are many factors that make it out of the goal. This prospective, single-blind, randomized study was designed to evaluate the effect of genotype-based warfarin dosing compared with standard warfarin dosing in Korean patients with mechanical cardiac valves. Patients were assigned to either the genotype-based dosing group or the standard dosing group using stratified block randomization. The genotype-based dosing equation was adopted from a previous study which included *VKORC1* rs9934438, *CYP2C9* rs1057910, *CYP4F2* rs2108622, and age. Primary outcomes included the percentage of time in the therapeutic range (pTTR): i) during the first week following initiation of warfarin therapy, ii) during hospitalization and iii) until the first outpatient visit.

1. **General information**
   1. **Protocol title, protocol identifying number and date**

- Protocol title: Comparative study on standard and pharmacogenetic-guided initial dosing of warfarin in patients with prosthetic heart valves
- Protocol identifying number: KCT0004586
- Date: 12/30/2019
  1. **Name and address of the sponsor/funder**

None.

- 1. **Name and title of the investigator(s) who is (are) responsible for conducting the research, and the address and telephone number(s) of the research site(s), including responsibilities of each**
- Name and title of the investigators: [name] (Professor), [name] (Professor)
- Address and telephone number of the research site
- Yonsei University Medical Center, [name] ([contact])
- Ewha Womans University, [name] ([contact])
  1. **Name(s) and address(es) of the clinical laboratory(ies) and other medical and/or technical department(s) and/or institutions involved in the research**

None.

1. **Rationale & background information**

Warfarin is a drug that has a narrow therapeutic range and shows individual differences in dose-response, and is influenced by various factors of patients such as interaction with various drugs, diet, and disease state [1-3]. The anticoagulant effect can change, which is why the drug needs special monitoring [4]. INR is ideal for being within the therapeutic range, but there are many factors that make it out of the goal.

Pharmacogenomics of warfarin is being actively investigated around the world, and an organization called the International Warfarin Pharmacogenomics Consortium (IWPC) has been created to study this [5]. To date, research on warfarin and genotyping has been published in the United States, Japan, and other countries, and recently, studies on Koreans are beginning to be published. We have identified genetic and non-genetic factors that influence the maintenance of patients undergoing heart valve replacement and have established a dose-prediction prediction system based on these factors [6].

1. **References (of literature cited in preceding sections)**

[1] Tiede DJ, *et al.* Modern management of prosthetic valve anticoagulation. Mayo Clin Proc 1998;73:665-80.

[2] Hirsh J. Oral anticoagulants: Mechanism of action, clinical effectiveness, and optimal therapeutic range. Chest 2001;119:8S-21S.

[3] Gage BF, *et al.* Management and dosing of warfarin therapy. Am J Med 2000;109:481-8.

[4] Rose JP, *et al.* Warfarin sensitivity after mechanical heart valve replacement. Pharmacotherapy 1998;18:856-9.

[5] Klein TE, *et al.* Estimation of the warfarin dose with clinical and pharmacogenetic data. N Engl J Med 2009;360:753-64.

[6] Lee KE, *et al.* Effects of CYP4F2 gene polymorphisms on warfarin clearance and sensitivity in Korean patients with mechanical cardiac valves. Ther Drug Monit 2012;34:275-282

1. **Study goals and objectives**

To investigate whether initial doses according to VKORC1, CYP2C9, and CYP4F2 genotypes are safer and more effective than conventional empirical doses in patients undergoing prosthetic valve replacement surgery and taking warfarin for the first time.

1. **Study design**

- Type of study: Interventional study (a prospective, single-blind, randomized study).
- Research population: Those who underwent cardiac valve replacement and taking warfarin.
- Inclusion criteria: Patients who require more than 3 months of warfarin after surgery for heart valve replacement.
- Exclusion criteria:

1) Minors under 20 years old

2) Patients with serious liver or kidney disease

3) Patients with cancer

4) Patients with risk of bleeding such as gastric ulcer.

1. **Methodology**
   1. **Intervention**

In this study, after receiving informed consent from the patient, 5 mg or 2.5 mg (age 65 or older or less than 50 kg) was administered to the standard dose group after being assigned to two groups of genotype and standard dose groups using a random table. Blood samples are taken at an outpatient visit before surgery, and a genetic test is performed therefrom.

- 1. **Procedures**
- Genotyping: Genotyping for *CYP2C9* (rs1057910), *VKORC1* (rs9934438), and *CYP4F2* (rs2108622) was performed using peripheral blood samples collected prior to the heart valve replacement surgery. Genomic DNA was isolated from EDTA-blood samples using the QIAamp DNA Blood Mini Kit (QIAGEN GmbH, Hilden, Germany) according to the manufacturer’s protocol. The TaqMan genotyping assay was conducted using the real time PCR system (ABI 7300, ABI, Forster City, CA, USA) according to the manufacturer’s protocol.
- Initial warfarin dose estimation: The model yielded the following equation: estimated initial warfarin dose (mg) = 11.305 - 2.082 x (number of *VKORC1* rs9934438 T allele) - 1.615 x (number of *CYP2C9* rs1057910 C allele) - 0.037 x age (year) + 0.983 x (*CYP4F2* rs2108622 AA=1, GA or GG = 0).
- International normalized ratio (INR): INR readings were checked on a daily basis during hospitalization and subsequently according to treating physician preferences.
  1. **Measurements**
- International Normalized Ratio (after warfarin start at day 1-7, week 2, 6, and three month later)
- Time until therapeutic INR (within study period)
- bleeding complication (within study period)
  1. **Randomization**

Patients were assigned to either the genotype-based dosing group or the standard dosing group using stratified block randomization. Strata were defined as a combination of sex (male vs. female) and age (≥65 vs. <65 years); the block size was 6 subjects and patients were blinded to their assigned arm.

- 1. **Blinding**

The patient is blind to the intervention.

- 1. **Stopping rules**
- Patients were excluded if they stopped using the drugs or did not adhere to the study protocol.
- The study would be terminated early if there were serious safety issues.
  1. **Graphic outline**

[figure not shown]

1. **Safety considerations**

The most common and significant adverse events of warfarin is bleeding mainly due to an over-anticoagulation. Bleeding symptoms include gum bleeding, hematuria, bloody stool, nasal bleeding, or hemoptysis. Other adverse events include nausea, vomiting, abdominal pain and loss of appetite. If the symptoms (mentioned above) or all other complaints, which occur during or after the treatment, the administration should be stopped immediately.

1. **Follow-up**

- INR: after warfarin start at day 1-7, week 2, 6, and three month later
- Time until therapeutic INR: within study period
- Bleeding complication: within study period

1. **Data management and statistical analysis**
   1. **Data management**

Appropriate computer programs will be run to verify the accuracy of the database.

- 1. **Statistical analysis**

In comparing the two groups, the time taken to reach the target INR (2.0-3.0) was constructed by using the Kaplan-Meier method to construct a survival curve and comparing the time-to-group reach by the log-rank test. Analysis of the number of patients reaching the target INR and the occurrence of adverse events (INR≥4, vitamin K use, bleeding, thrombogenesis, myocardial infarction, stroke, death) on days 1-7, 2, 6, and 3 months using Chi-squared test. A p-value of < 0.05 was considered statistically significant. All analyses were performed with the IBM SPSS Statistics version 20 Software (International Business Machines Corp., New York, USA).

1. **Quality assurance**

The collected data will be monitored and reviewed every 3 month by the investigators. The chief investigator is responsible for data verification to assess the accuracy, completeness, or representativeness of study data by comparing the study data to original data sources (e.g., medical records).

1. **Expected outcomes of the study**

The benefits of this research extend to potential improvements in the warfarin treatment. Results of this study could be used to develop and implement individually tailored intervention strategy especially for determining the initial dose of warfarin.

1. **Dissemination of results and publication policy**

The chief investigator is [name] and she had overall responsibility for a study, whereas Principal Investigator for this clinical study is [name] and he had direct clinical responsibility for patients.

1. **Duration of the project**

- IRB approval: Sep 2012 to Dec 2012
- Enrollment: Jan 2013 to Aug 2017

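### Randomisation is stratified by sex and age 65, but the named log-rank and chi-squared tests do not use the strata, and the control dose steps at the same age cut

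*Protocol*

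**What the plan says.** **Allocation.** Protocol, Methodology, Randomization: "Strata were defined as a combination of sex (male vs. female) and age (≥65 vs. <65 years); the block size was 6 subjects".

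**Analysis.** Protocol, Statistical analysis: time to the target INR is described by Kaplan-Meier curves, "comparing the time-to-group reach by the log-rank test". The number of patients reaching target and the adverse events are compared "on days 1-7, 2, 6, and 3 months using Chi-squared test". No strata, covariates or age-group results are mentioned. The section also fixes the significance level ("A p-value of < 0.05 was considered statistically significant") and the software.

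**Doses.** Protocol, Intervention: "5 mg or 2.5 mg (age 65 or older or less than 50 kg) was administered to the standard dose group". Procedures gives the genotype arm's dose as a linear equation: 11.305 mg, minus 2.082 per VKORC1 T allele, minus 1.615 per CYP2C9 C allele, minus 0.037 per year of age, plus 0.983 if CYP4F2 is AA.

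**Context.** The consent text says that after day 3 both arms are adjusted by INR in the same way, and gives 200 as the expected number of patients. The Project summary names percentage of time in therapeutic range (pTTR) as the primary outcome. The two tests above therefore serve the time-to-INR and event comparisons, not pTTR.

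**The concern.** Two separate things are at stake.

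1. **Efficiency.** Blocking within strata balances the arms on sex and age. If those factors predict how fast a patient reaches target INR, a test that leaves them out does not use that balance. Its nominal type I error is protected, but it can be conservative and less powerful than a test stratified the way patients were allocated.

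2. **Interpretation.** The age cut that defines the strata is also the age at which the control dose halves, while the equation changes by only 0.037 mg per year. The size of the starting-dose contrast thus depends on the stratum, for a reason that lies in the comparator rule and not in genotype. The stated objective is to test doses chosen by VKORC1, CYP2C9 and CYP4F2 genotype. One pooled comparison cannot tell genotype guidance from the control arm's age step, and this applies equally to INR of 4 or more and to bleeding.

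**Working it through.** **Is there a figure to reproduce?** No. The protocol gives 200 patients without a power, effect size or rate. For orientation only, with an assumed hazard ratio (HR) of 1.5 and all 200 patients reaching target, Schoenfeld's formula gives Φ(√200 × ln 1.5 / 2 − 1.96) = Φ(2.867 − 1.96) = Φ(0.907) ≈ 0.82.

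**Step 1: dose contrast at the stratum boundary.** This uses protocol figures only. Ratio = equation dose ÷ standard dose, for patients of at least 50 kg (5 mg at 64, 2.5 mg at 65).

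For VKORC1 TT, no CYP2C9 C allele, CYP4F2 not AA: dose = 11.305 − 2 × 2.082 − 0.037 × age = 7.141 − 0.037 × age.
- Age 64: 7.141 − 2.368 = 4.773 mg; ÷ 5 = 0.95.
- Age 65: 7.141 − 2.405 = 4.736 mg; ÷ 2.5 = 1.89.

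| T alleles | C alleles | CYP4F2 | Ratio at 64 | Ratio at 65 |
|---|---|---|---|---|
| 2 | 0 | not AA | 0.95 | 1.89 |
| 2 | 0 | AA | 1.15 | 2.29 |
| 2 | 1 | not AA | 0.63 | 1.25 |
| 1 | 0 | not AA | 1.37 | 2.73 |
| 0 | 0 | not AA | 1.79 | 3.56 |

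In general the step is 2 × (1 − 0.037 ÷ dose at 64). Over all 18 genotype combinations the dose at 64 runs from 1.543 mg (TT, two C alleles, not AA) to 9.92 mg (no T, no C, AA). The step therefore runs from 2 × (1 − 0.0240) = 1.95 to 2 × (1 − 0.0037) = 1.99. The level of the ratio depends on genotype; the near-doubling does not.

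**Step 2: power under a common treatment effect.** Everything here is assumed except the strata, the block size and N: 200 patients, blocks of 6 in four strata, 35% aged 65 or older, sex HR 1.2, treatment HR 1.5, daily times to day 14, two-sided 0.05, 2,500 runs per scenario (error about 1 point).

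| Age-group HR | Plain log-rank | Stratified | Loss (points) |
|---|---|---|---|
| 1 | 78% | 78% | 0 |
| 1.5 | 76% | 77% | 1 |
| 0.67 | 73% | 75% | 2 |
| 2 | 75% | 80% | 5 |
| 0.5 | 69% | 74% | 5 |
| 3 | 68% | 76% | 8 |
| 0.33 | 61% | 73% | 12 |

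The plain test's type I error falls to 3.0-3.3% at age HR 3 or 0.33; the stratified test stays at 4.4-5.2%. A second simulation (follow-up to 90 days, 800 runs, error 1-2 points) gave plain against stratified power of 77% vs 79% at age HR 1.5 and 73% vs 79% at age HR 2. With neither age nor sex prognostic it gave 83% vs 80%, so stratifying can cost a little. Its plain type I error was 4.8-5.3% for age HRs from 1 to 2.

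**Step 3: power if the effect exists only at 65 or older.** The second simulation, with treatment HR 2 at 65 or older and 1 below:

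| Age-group HR in controls | Plain | Stratified |
|---|---|---|
| 2 | 10% | 28% |
| 1.5 | 14% | 29% |
| 1 | 25% | 31% |
| 0.67 | 39% | 32% |
| 0.5 | 49% | 33% |

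The sign changes according to whether older control patients reach target faster or slower than younger ones. The documents do not say which.

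**The case against.** **The section is silent; it does not prohibit.** It never says that the tests are unstratified, and an unseen analysis plan could add the strata. That is fair, and a reader should not infer that the protocol forbids stratification. But the section does more than stay silent: it fixes named tests, a level and the software. Improving a method that is stated is a legitimate comment.

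**A reader might infer that the tests are invalid or that power is certainly lost.** Neither is supported. Type I error stays at or below about 5%. The loss is negligible unless age is clearly prognostic, which the documents do not establish, and Step 3 shows that it can turn into a gain.

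**A reader might infer a contrast of 1.7-1.9 above 65 and near 1 below.** That describes one genotype (TT, no C allele, not AA). At 65 the other genotypes tabulated range from 1.25 to 3.56, and no genotype frequencies are given. Patients under 65 weighing less than 50 kg also receive 2.5 mg in the control arm; for that same genotype at age 50 the ratio is then 5.291 ÷ 2.5 = 2.12.

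**The contrast is brief.** INR-guided adjustment is common to both arms after day 3, which limits how long the starting-dose difference lasts. This stands.

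**Stratifying does not remove the mixing.** Correct: a stratified log-rank or Cochran-Mantel-Haenszel test still gives one averaged effect. Only results by age group address that, and with about 0.35 × 200 = 70 patients assumed to be 65 or older an interaction test would be weak.

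**Age is already declared.** The Project summary says that the equation includes age. It does not say that the control rule steps at the stratification cut, which is what affects interpretation.

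**Conclusion.** The point holds in moderate form. The named tests omit the randomisation strata. They remain valid, and the avoidable power loss under a common effect is about 0-2 points with weak and 5-12 points with strong age prognosis. Those sizes rest on an assumed HR of 1.5, 35% aged 65 or older, and the assumed age and sex effects.

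The dose finding needs no assumed rates: in patients of at least 50 kg the starting-dose ratio rises 1.95- to 1.99-fold between 64 and 65 for every genotype. A pooled result therefore averages two different dose contrasts. A reader might go further and conclude that the pooled effect is wrong or that any difference is due to the age step. The documents do not show that; they show only that the pooled result cannot separate the two sources. This should be fixed, but it does not undermine the trial's inference.

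**What to change.** - Stratify the log-rank test by the four randomisation strata.
- Use Cochran-Mantel-Haenszel tests for the binary outcomes, with an exact or unstratified test, under a rule set in advance, where events such as stroke or death are too sparse.
- Include the strata in any model for pTTR. Adjustment for genotype is optional.
- Report the effects for 65 or older and under 65 separately, with an interaction estimate labelled as supportive.
- Word the conclusion as a comparison of the age-plus-genotype equation with the 5/2.5 mg rule, and not as an effect of genotype alone.

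Cost: wording and code only, since sex, age and genotype are already collected. The downsides are a slight loss of information in small strata and an interaction test with low power.

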1. **Risk of the study and stop rules**

In genotype-based dosing group, you may receive a higher dose than the empirical dose of warfarin and it might result in bleeding or thrombogenesis. If the patients show poor compliance, or are willing to withdraw from the study, the study will be discontinued. The study would be terminated early if there were serious safety issues in the interim analysis (n=60 and/or 100).

1. **Research site, investigator, and total expected number of patients.**
2. Research site: Yonsei University Medical Center and Ewha Womans University
3. Principal investigator: [name]
4. Total expected number of patients: 200
5. Duration of the project: 60 months after IRB approval
6. **Methodology**

This study is to investigate whether genotype-based doses of warfarin are safer and more effective than conventional empirical doses. Patients, who voluntarily agree take part in this study, will be randomly assigned to receive genotype-based or standard dose of warfarin. In genotype-based dosing group, dose is decided by genotype, and after day 3, dose is adjusted by INR in the same way between two groups. For genotyping, we use a portion of the blood already collected for laboratory test under your agreement; therefore, additional visit is not needed. Blood samples will not be used for any other purpose other than this study. All information will be kept confidential.

1. **Information provided**

All information will be kept confidential, and information can be provided on request limited to yours. Information will be provide privately by the study staff in charge.

1. **Sample storing, handling and anonymization**

Collected samples are stored in deep freezer until 5 years after end of the study. Demographic and clinical information are locked with a security program that only the study staff will be able to access.

1. **Confidentiality**

All information will be kept confidential, and information will be collected without patient identifiers by assigning random number to each patient. When the results are published, your identity will not be disclosed.

However, medical files can be viewed by authorized persons as part of monitoring personnel, audit personnel, ethics review committee, and health authorities to inspect the procedures and reliability. By signing this consent form, you permit us to view your medical records.

1. **Voluntary participation/withdrawal**

